## Abstract

**Background:**

The World Health Organization recommends pre-exposure prophylaxis (PrEP) for all populations at substantial risk of HIV infection. However, at-risk women very rarely use PrEP in France—this represents a critical issue among migrant women sex workers (MWSWs). Previous studies on PrEP use among women sex workers or migrants focused on individual or social determinants of motivation. However, operational studies in real-word settings using a holistic population approach to maximize PrEP adherence among MWSWs are lacking.

**Objective:**

FASSETS (ie, “Favoriser l’Accès à la Santé Sexuelle des Travailleuses du Sexe”; English: “facilitate the access to Sexual Health in women sex workers”) is a participative, multilevel, mixed methods study aiming to improve global knowledge of and access to sexual health care and PrEP among MWSWs through targeted empowerment strategies.

**Methods:**

This study comprises several phases: (1) phase 1: an initial qualitative study combining semistructured interviews, informal interviews, and participative observations will be performed among MWSWs, local community nongovernmental organizations, and institutions providing sexual reproductive health services to identify the determinants of PrEP access among MWSWs and for respondent-driven sampling (RDS); (2) phase 2: the size of the hidden MWSW population is estimated in Marseille through capture-recapture (the RDS survey will serve as “recapture”); (3) phase 3: a longitudinal cohort will be formed through RDS to represent the MWSW population with a goal of 150 inclusions—this cohort will be followed up for 12 months, and sequential questionnaires exploring medical history; knowledge of sexual health, HIV, and sexually transmitted infections; migration route; and current living conditions will be administered at inclusion (month 0) and months 3, 6, and 12 to measure the following interventional phase’s outcomes; and (4) phase 4: an interventional study with community empowerment actions about sexual health and PrEP will be conducted with community health workers; standardized questionnaires and semistructured interviews, observations, and focus groups will highlight MWSWs’ experiences with empowerment resources, concerns about sexual health, and especially PrEP use or uptake, and we will evaluate whether and how community-adapted empowerment actions conducted by community health workers are effective in increasing access to sexual health, prevention and screening of sexually transmitted infections, and PrEP knowledge and access among MWSWs.

**Results:**

Recruitment commenced on March 1, 2022. We estimate the follow-up period to end on September 30, 2023.

**Conclusions:**

This multiphase study will provide robust evidence about the magnitude of the MWSW population in Marseille (the second largest town in France) and their current conditions of living, access to and knowledge of sexual health, and PrEP access. Using a mixed methods analysis, we will investigate whether individual and collective community health empowerment approaches can facilitate access to PrEP and its initiation, use, and adherence in this vulnerable population.

**International Registered Report Identifier (IRRID):**

DERR1-10.2196/42844

## Introduction

In contrast to the population of men who have sex with men, where HIV incidence has decreased owing to pre-exposure prophylaxis (PrEP—taking antiretroviral drugs to prevent HIV infection), estimates of HIV incidence have not decreased in migrant populations in France and other European countries [1,2]. Indeed, the highest incidence of HIV infection has been currently reported in migrants in France [2]. Moreover, when living with HIV, migrants also tend to be diagnosed later than nonmigrants [3,4]. In this context, a recent French study has shown that a majority of migrants (58%) contracted HIV within 6 years after arrival [5], confirming previous results showing that migrants living with HIV in Europe frequently contracted the virus post migration [6-8]. In this French study, HIV acquisition after migration was linked to short or transactional partnerships and the lack of a residence permit [5]. These results highlight the economic and social determinants of HIV exposure in this population. Another study showed that in France, the majority of migrants do not know about PrEP as a tool for HIV prevention [9].

HIV prevalence among cis- or transgender women engaged in transactional sex (women sex workers [WSWs]) is substantially higher than that in similarly aged women worldwide [10,11]. Consequently, migrant WSWs (MWSWs) are at a particularly high risk of HIV infection, and progress toward the global target of HIV elimination will not be possible without interventions and programs aimed at them.

Previous studies on HIV prevention programs have specifically targeted WSWs, and PrEP has emerged as a potentially effective option for HIV prevention in this population, with most studies being performed in transitional countries [12]. PrEP is highly effective in reducing HIV incidence in this population with appropriate individual compliance [13]. Unfortunately, 2 PrEP trials among cisgender women in Africa were stopped early due to suboptimal adherence [14,15]. The subject of adherence and its determinants is of tremendous importance in this population [12]. As with HIV risk factors, determinants of PrEP use in WSWs arise from multiple social and biological factors [9,14,16]. MWSWs face structural factors associated with a precarious immigration status, migration, and occupation-related marginalization [11]. A systematic review among WSWs has stressed the need for comprehensive care in order to increase the use of and adherence to PrEP [12,17]. However, few studies have investigated how to implement community-based interventions to promote PrEP access and health equity within this vulnerable population [11]. Indeed, there is a need to develop interventions with a holistic approach, including specific clinics and social services [12,18]. Another key element is to implement a prevention intervention based on community empowerment, in which MWSWs take collective ownership of knowledge of and resources about sexual health [19].

In France, as in other European countries and the United States, women represent a minority of PrEP users (less than 3%) [20-22]. Marseille is France’s second largest city and one of the poorest (with 200,000 people living with less than €1000 [US $1086.26] per month) located on the Mediterranean coast [23]. In 2018, overall 12% of Marseille’s population (192,330 inhabitants) was born abroad and statistically considered a migrant population with 28% of them born in northern Africa and 14% of them born in sub-Saharan Africa [24]. These figures do not take into account undocumented migrants. Among 2197 people consulting for PrEP at the 10 medical centers for sexual health and prevention (managed by the departmental council of the Bouches du Rhône—an area of Marseilles and its suburbs) between 2016 and 2022, only 7 were MWSWs [25].

The objectives of the FASSETS (Favoriser l’Accès à la Santé Sexuelle des Travailleuses du Sexe) study are to (1) analyze the individual and structural determinants of the access to sexual health care and notably PrEP among MWSWs working in Marseille, (2) estimate the size of the MWSW population in Marseille, and (3) follow up with a representative cohort of 150 MWSWs to evaluate the effectiveness of a holistic approach based on community empowerment interventions targeting MWSWs to improve PrEP use.

For this purpose, we designed a mixed methods study comprising the following: (1) a study in the field with community health workers (CHWs) evaluating the determinants for the access to PrEP, (2) a capture-recapture method with respondent-driven sampling (RDS) to estimate the size and characteristics of a hidden and stigmatized population, (3) formation of a longitudinal cohort of MWSWs that will be followed up for 12 months, and (4) an intervention study involving CHWs to apply an empowerment strategy and evaluate its results with regard to the number of MWSWs taking PrEP at the end of the follow-up period.

## Methods

### Overview

Phase 1 of the FASSETS study is a qualitative multilevel evaluation of facilitators and barriers to PrEP access for MWSWs in Marseille, which will last 12 months before the intervention begins (Figure 1).

Phase 2 will be a capture-recapture study to evaluate the size of the MWSW population in Marseille (Figure 1).

Phase 3 will involve the formation and follow-up of a representative cohort of 150 MWSWs.

Phase 4 will be the community empowerment intervention by CHWs provided to the 150 MWSWs of the cohort recruited through RDS (Figure 1).

The intervention by CHWs will consist of facilitating knowledge and PrEP uptake but also more generally to facilitate access to health care and social services as needed, using an individual and longitudinal follow-up and collective empowerment actions.

**Figure 1 figure1:**
[figure not shown]
Mixed methods model of intervention analysis. PrEP: pre-exposure prophylaxis; RDS: respondent-driven sampling.

### Objectives of the Different Phases of the Study

Phase 1 will describe the determinants of PrEP uptake in MWSWs with a multilevel approach including individual, collective, and institutional analysis.

Phase 2 will determine the size of the MWSW population in Marseille.

Phase 3 will describe attitudes, knowledge, and practices of sexual and reproductive health (SRH) among MWSWs, health care pathways and mobility, testing for sexually transmitted infections, and prevalence and frequency of screening in the MWSW population at month 0 and their evolution during follow-up.

Phase 4’s primary objective is to analyze access to PrEP and retention in care through a community empowerment follow-up of MWSWs. Secondary objectives will be to document individual and collective empowerment tools for MWSWs and to describe CHW interventions for MWSWs.

### Key Outcomes for Each Phase of the Study

The key outcomes of phase 1 will be the analysis of the verbatim responses of MWSWs and institutional actors about the determinants of PrEP use, those of phase 2 will be the estimated number of MWSWs in Marseille, those of phase 3 will be the number of MWSWs included in the longitudinal study and quantitative analysis of the questionnaire data, and those of phase 4 will be the number of consultations for sexual health, access to rights, and PrEP uptake among MWSWs before and after the interventional phase.

### Study Population

The FASSETS study will take place in Marseille, which is the second largest city in France, and a significant proportion of its population has precarious living conditions [26]. The FASSETS study was developed in collaboration with the nongovernmental organization (NGO) AIDES and a Nigerian community NGO for women (The Truth), which provides HIV prevention and testing services to MWSWs.

### Phase 1: Qualitative Assessment

Qualitative data collection will be carried out separately with a trained qualitative researcher. Qualitative interviews will be conducted following semistructured interview guides in private with selected participants representative of the cohort, in focus groups, and in a multilevel assessment with doctors and social workers in the field. These interviews will be carried out to document the determinants for PrEP access in MWSWs.

### Phase 2: Estimation of the Sample Size of the Hidden Population of MWSWs by Capture-Recapture

Population size estimation is a challenge because the MWSWs are hidden and difficult to reach. Hence, capture-recapture is recommended to estimate the size of the MWSW population in Marseille [27,28]. The estimation will be based on the following equation:

*N*=(*n*1×*n*2)/*m*

where *n*1 is the number of MWSWs who received a token (capture), *n*2 is the number of MWSWs included in the RDS study (recapture), and *m* is the number of participants common to both groups (MWSWs with a token). Tokens (safety whistle: a little emergency whistle with a flashlight) will be distributed over a period of 15 days by the NGOs and institutions but also directly to the MWSW network. Indeed, distribution of safety whistles will serve as a first “capture” and the RDS survey will serve as “recapture.” When participants visit the center for RDS enrollment, they will be asked if they had received a safety whistle; if they answer yes, the research team will ask them to identify the safety whistles from a group of photographs depicting different safety whistles. If the participants correctly identify the safety whistles from the photographs, they will be included as having received a safety whistle.

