### Phase 3: Representative Cohort Formation Through RDS and Follow-up

The inclusion criteria are being a cis- or transgender woman older than 18 years, self-reporting as having changed their sex for money or other resources during the past 12 months, having been born outside of France, living or working in the city of Marseille, and agreeing to participate in the study.

Numerous studies have demonstrated the effectiveness of RDS to engage adults in HIV research, particularly in stigmatized communities [29,30]. Initial RDS participants (ie, “seeds”) will be recruited for the study to achieve good representativeness in terms of the type of community or nationality, sex work (eg, indoor, outdoor, via the internet), place of residence in Marseille, and gender (cis- or transgender women). The prior qualitative study will make it possible to clearly define the characteristics of representativeness. Approximately 150 participants are expected to be enrolled in the cohort. At the beginning, participants will be offered 3 coupons. Participants who meet the eligibility criteria will be provided with a food coupon worth €10 (US $10.86) for completing each part of inclusion and follow-up (at months 3, 6, and 12), and another food coupon worth €10 (US $10.86) for each eligible and participating peer recruited. In addition, FASSETS study participants will be given public transport tickets, free condoms, and lubricating gel.

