### Data Collection

Upon enrollment and at months 3, 6, and 12, participants will be asked to complete a structured survey administered by a CHW. The survey will include questions regarding network size for RDS weighting. These will include questions about the token given at the time of data capture. Individual data including sociodemographic characteristics; sexual practices; knowledge and behavior; HIV testing history; medical history; PrEP knowledge, adherence, and compliance; contraception; drug and alcohol use; mental health (including Perceived Stress Scale-10 scores); quality of life; literacy; social support; being subjected to racism; stigmatization or violence during the past 12 months; and mobility will be collected. Other more structural determinants will be collected as follows: residence permits, health insurance, housing conditions, and food security (Table 1). Indeed, such structural determinants are previously described to have a significant impact on health care access among sex workers [42]. The semistructured questionnaire will explore the barriers and levers to accessing PrEP among MWSWs. The instrument or interview guide will attempt to understand how PrEP fits into women’s needs, care pathways, and mobility. Representation of MWSWs’ PrEP uptake among caregivers and which mechanisms are (or are not) implemented by social institutions to facilitate access to prevention and care for MWSWs (Table 1).

Type, objective, and number of actions of mediation in terms of prevention, support, or access to health care or social services will be self-reported by CHWs.

CHWs will use encrypted and secure survey software to report the MWSWs’ responses to the questionnaires and to monitor their actions of mediation. All electronic questionnaires will be forwarded to a database that is managed and hosted by SESSTIM (Inserm laboratory in Marseille). Each staff member will have a secure individual account.

Databases of all NGOs and institutional screening and PrEP centers of Marseille will be retrospectively analyzed to describe the HIV status and to assess PrEP characteristics among migrants and women in Marseille.

**Table 1 table1:** Data collection tools and timing.

Method	Timing	Population	Data collected

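### Phase 2 fixes the uncorrected Lincoln-Petersen ratio for population size, which overstates N on average when token overlap is small; the Chapman form nearly removes this from the same data.

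*Protocol article*

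**What the plan says.** The phase 2 section of the protocol article introduces its estimator with "The estimation will be based on the following equation" and gives N = (n1×n2)/m. Here n1 "is the number of MWSWs who received a token (capture"), n2 is the number of women included through respondent-driven sampling (RDS), and m "is the number of participants common to both groups (MWSWs with a token"). A woman counts towards m only if she reports having received the safety whistle and then picks it out from photographs. The tokens "will be distributed over a period of 15 days by the NGOs and institutions but also directly to the MWSW network".

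On n2, the phase 3 section says: "Approximately 150 participants are expected to be enrolled in the cohort". No number of tokens, expected overlap or anticipated population size is given.

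The objectives section states: "Phase 2 will determine the size of the MWSW population in Marseille". The section on key outcomes lists the estimated number as the only outcome of phase 2, and the abstract's conclusions announce: "This multiphase study will provide robust evidence about the magnitude of the MWSW population in Marseille".

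**The concern.** The stated equation is the simplest two-sample estimator, without a small-count correction. Under random recapture the mean of m is n1×n2/N, so putting that mean into the formula returns N. But the formula uses the observed m, and the average of 1/m is larger than 1 divided by the average of m. The ratio therefore runs high on average, and the excess grows as the overlap shrinks. At m = 0 it cannot be computed. This is separate from any bias due to peer recruitment, token channels or turnover in the population.

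The design leaves room for a small overlap: about 150 women in the recapture sample, a 15-day distribution, and a photograph test before a token is counted. One woman more or less can then move the answer considerably. With n1 = 100 and n2 = 150, m = 8 gives 15,000/8 = 1875 and m = 7 gives 15,000/7 = 2143. At stake is the accuracy of the single phase 2 outcome.

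**Working it through.** **Inputs.** n2 = 150 is the enrolment expected in the phase 3 section. N (500 to 3000) and n1 (50 to 300) are assumptions, since the article gives neither. There is no stated figure to reproduce.

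**Model.** With every capture-recapture assumption true, m follows a hypergeometric distribution (N women, n1 with tokens, 150 drawn), with mean E[m] = 150×n1/N.

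**Estimators.**
- Stated: n1×150/m, averaged over m > 0 because it is undefined at m = 0.
- Chapman: (n1+1)(151)/(m+1) − 1, averaged over all m.

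**Results.** Exact expectations; RMSE is the root mean squared error in women.

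| E[m] | N | n1 | Stated: bias | Stated: RMSE | Chapman: bias | Chapman: RMSE |
|---|---|---|---|---|---|---|
| 45 | 1000 | 300 | +1.4% | 122 | 0.0% | 117 |
| 30 | 1000 | 200 | +2.4% | 165 | 0.0% | 154 |
| 15 | 1000 | 100 | +5.8% | 284 | 0.0% | 239 |
| 15 | 2000 | 200 | +6.4% | 602 | 0.0% | 502 |
| 10 | 3000 | 200 | +11.3% | 1404 | 0.0% | 1002 |
| 7.5 | 1000 | 50 | +14.9% | 589 | 0.0% | 379 |
| 7.5 | 2000 | 100 | +16.4% | 1268 | 0.0% | 802 |
| 5 | 3000 | 100 | +26.7% | 2622 | −0.5% | 1551 |
| 3.75 | 2000 | 50 | +29.9% | 1792 | −1.7% | 1114 |
| 2.5 | 3000 | 50 | +24.3% | 2261 | −7.0% | 1655 |

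The bias of the stated ratio drops in the last row only because the samples with m = 0, which would have given the largest estimates, are excluded. The probability of m = 0 is 7.5% there, 1.9% at E[m] = 3.75, 0.5% at 5, and about 0.03% or less from 7.5 upwards.

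**Single data sets, n1 = 200.**
- m = 5: stated 30,000/5 = 6000; Chapman 201×151/6 − 1 = 5058.
- m = 15: stated 2000; Chapman 1896.
- m = 30: stated 1000; Chapman 978.
- m = 0: stated undefined; Chapman 201×151/1 − 1 = 30,350, a finite number without practical meaning.

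**Dependence, for scale.** Take N = 1000 and n1 = 200, and let token holders be twice as likely as other women to enter the RDS sample. The recapture probability for the others is 150/(2×200 + 800) = 0.125, so E[m] = 200×0.25 = 50. At that overlap the stated ratio gives 30,000/50 = 600 and Chapman 30,351/51 − 1 = 594. If token holders are half as likely, E[m] = 16.7 and the values are 1800 and 1717. Neither form corrects this.

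**The case against.** The equation is a standard estimator with correctly defined terms, and an article may leave refinements to the full protocol or analysis plan. That holds for an interval or a rule for m = 0, and their absence is not raised here. It does not hold for the point estimator, which the article states explicitly.

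The premise of small overlap is assumed. This stands. The 150 is an expectation and not a ceiling, the 15-day window does not limit n1, and tokens go out through several channels. A reader might infer that the phase 2 estimate will be inflated by 15% to 30%. The article does not support that, because nothing in it predicts an expected overlap of 7.5 or less. At 30 the mean bias is about 2%, against an RMSE of about 15% to 17% of N for the stated ratio.

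A reader might also infer that Chapman removes the bias at no cost. It does not. It is exactly unbiased only if n1 + n2 is at least N, and it is biased low at very small overlap. Its median also tends to lie below N: at N = 2000 and n1 = 200 the medians are 2000 for the stated ratio and 1896 for Chapman. At N = 2000 and n1 = 100 a single Chapman estimate falls below N about 64% of the time, against 48% for the stated ratio. Chapman is better on mean bias and RMSE in every scenario tabulated, but not on every criterion.

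Finally, the correction is second-order. Recapture is by peer recruitment, and tokens travel partly through the women's own network. The Data Collection section says "The survey will include questions regarding network size for RDS weighting", yet the equation uses raw counts. If token holders are more likely to be recaptured, both forms run low, and Chapman slightly lower. This stands as a limit on what the change achieves.

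**Conclusion.** The concern holds in a conditional form. The article commits phase 2's key outcome to a ratio that overstates N on average at small overlap, although an estimator with lower RMSE is available from the same three counts. Under random recapture of 150 women, the mean bias is about +2% at an expected overlap of 30, +6% at 15, +15% to +16% at 7.5, and +24% to +30% at 2.5 to 5. Which of these applies cannot be told from the article, since N, n1 and the overlap are all assumed here. If the overlap reaches 30 or more, the choice hardly matters. Adopting Chapman would not by itself secure the robust evidence that the abstract announces, because dependence between token distribution and RDS recruitment can produce a larger error in either direction.

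**What to change.** In the phase 2 section, replace the equation by the Chapman estimator, N = (n1+1)(n2+1)/(m+1) − 1, with n1, n2 and m defined as now. State that if m = 0 the population size will be reported as not estimable.

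The cost is one line of analysis wording. No new data or fieldwork is needed, and the change can still be made after recruitment has begun. The statistical price is a slightly lower point estimate, with a median somewhat below N and a downward bias at very small overlap (−1.7% at an expected overlap of 3.75, −7.0% at 2.5 in the scenarios above). The text should also say that the correction deals only with the small-count bias and leaves any dependence between token distribution and RDS recruitment untouched.

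### The population size formula uses unweighted RDS counts although network size is collected for weighting, so N is at risk of bias of unsettled sign and size

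*Protocol article*

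**What the plan says.** The Phase 2 section fixes the estimator: "The estimation will be based on the following equation", followed by N = (n1 × n2)/m. Each term is defined there as a count. n1 "is the number of MWSWs who received a token (capture"; n2 "is the number of MWSWs included in the RDS study (recapture"; m "is the number of participants common to both groups (MWSWs with a token".

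The tokens are safety whistles, which "will be distributed over a period of 15 days by the NGOs and institutions but also directly to the MWSW network". Overlap is scored by self-report and a photograph test: "If the participants correctly identify the safety whistles from the photographs, they will be included as having received a safety whistle".

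The Phase 3 section describes the seeds as the first participants in the RDS. They "will be recruited for the study to achieve good representativeness in terms of the type of community or nationality", among other characteristics. About 150 women are expected to enrol, and participants are at first offered three coupons for recruiting peers. The Data Collection section says that the survey will ask about network size so that RDS weights can be formed, and that it will also ask about the token.

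Population size is the second of the three objectives in the Introduction and the key outcome of phase 2. The Abstract concludes: "This multiphase study will provide robust evidence about the magnitude of the MWSW population in Marseille".

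**The concern.** The ratio m/n2 has one task: to estimate the share of all eligible women who received a token. Dividing n1 by that share gives N. This works if inclusion in the second sample is unrelated to having a token.

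RDS does not give equal inclusion chances. Women with more contacts have more routes to a coupon and are over-represented in the raw sample. If token receipt also varies with the number of contacts, the raw share is off and N moves the opposite way. Part of the distribution runs directly through the network, so a link is plausible. The study evidently expects to need weights, since it collects network size for them, yet its formula for N has no weight term.

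Seeds raise a smaller form of the same problem. They are chosen by the study team, so their token share need not resemble that of women recruited by peers.

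At stake is the phase 2 result itself, which the article presents as robust evidence.

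**Working it through.** The article gives no value for n1, m or N, so there is no figure to reproduce. From the document: the formula and n2 of about 150. Everything else below is assumed for illustration.

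**1. Effect of leaving out the weights.** Assume N = 1000, with half the women having the smaller network size and half the larger. In each row the mean token chance is 20%, so n1 = 200. With inclusion proportional to network size, sizes 5 and 15 make up 5/20 = 0.25 and 15/20 = 0.75 of the sample; sizes 5 and 10 make up 1/3 and 2/3. The formula then gives N = n1/(raw share).

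| Network sizes | Token chances | Raw share m/n2 | N from the formula |
|---|---|---|---|
| 5, 15 | 10%, 30% | 0.25×0.10 + 0.75×0.30 = 0.250 | 800 (−20%) |
| 5, 10 | 10%, 30% | 0.033 + 0.200 = 0.233 | 857 (−14%) |
| 5, 10 | 15%, 25% | 0.050 + 0.167 = 0.217 | 923 (−8%) |
| 5, 15 | 20%, 20% | 0.050 + 0.150 = 0.200 | 1000 (0%) |
| 5, 15 | 30%, 10% | 0.075 + 0.075 = 0.150 | 1333 (+33%) |

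Weighting each participant by 1/(network size) in the first row gives (0.25×0.10/5 + 0.75×0.30/15)/(0.25/5 + 0.75/15) = 0.020/0.100 = 0.20, and N = 200/0.20 = 1000.

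**2. The same check in another form.** Let p be the true token share and k the ratio of mean network size in token holders to that in other women. The raw share is pk/(pk + 1 − p), and the formula's N divided by the true N is (pk + 1 − p)/k. With p = 0.30, this ratio is 1.35 at k = 0.67, 1.00 at k = 1, 0.77 at k = 1.5 and 0.65 at k = 2.

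**3. Seeds.** With s seeds of whom a share q hold a token, and a share p among the others, N with seeds divided by N without is 150p/[(150 − s)p + sq]. The number of seeds is not stated. For s = 8 and p = 0.30:
- all seeds hold a token: 45/(42.6 + 8) = 0.89;
- seeds hold tokens like the others: 1.00;
- no seed holds a token: 45/42.6 = 1.06.

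**4. Width of the interval.** Assume n1 = 300, n2 = 150 and m = 45. The Chapman estimate is 301×151/46 − 1 = 987. Its variance is (301×151×255×105)/(46²×47), about 12,237, which gives a 95% interval of 770 to 1204. Multiplying the variance by an assumed RDS design effect of 2 gives 680 to 1294; by 4, 553 to 1421.

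**The case against.** The strongest reply is that the article condenses a fuller protocol. It says that the estimate is based on the equation, and it plans the network-size and token questions for the same survey, so a weighted token share may be intended. The data are indeed planned, which makes the fix cheap. But the estimator is stated, not left open: its terms are defined as counts, and no section brings the weights into them.

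It can also be said that the direction is unknown. This is correct. NGOs and institutions hand out tokens too, and some NGOs and community health workers visit sex work sites, which may reach less connected women. A reader might infer that N is certainly biased, or certainly too low; the documents support neither.

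Other stronger readings also fail:
- **Repeat tokens inflate n1.** n1 is defined as women, not whistles. The article is silent on how distinct women are counted across channels, and silence there is no error.
- **Passed-on whistles inflate N.** Overlap is scored by receipt and recognition, not possession. A whistle passed to another eligible woman could add to m without adding to n1, which lowers N.
- **Seeds are counted by rule.** No section says so. It follows only from reading the definition of n2 together with the description of seeds.
- **Population turnover raises N by a known amount.** Recruitment began on March 1, 2022, and follow-up is expected to end on September 30, 2023. With 12 months of follow-up this allows about 7 months of enrolment, but no recruitment length or turnover rate is given.
- **N is the denominator for PrEP coverage.** No section uses it so, and the phase 4 evaluation does not depend on it.

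**Conclusion.** The point holds in limited form. The formula as written estimates token coverage without bias from unequal RDS inclusion only if token receipt is unrelated to network size. The article does not state that condition, and its partly network-based distribution makes it doubtful. Otherwise N is at risk of bias whose sign and size the documents do not settle. Under the assumptions shown, the error runs from −20% to +33% in the two-group example, and it is zero when token chances are equal. Seeds add a smaller shift, from −11% to +6% with eight assumed seeds and a 30% token share, and none if seeds hold tokens as often as others. The claim of robust evidence needs the weighted estimator behind it. This is a cheap improvement to a stated objective and does not touch the phase 4 evaluation.

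**What to change.** State the phase 2 estimator as N = n1/p_w. Here n1 is the number of distinct women given a token, and p_w is the RDS-weighted share of non-seed participants who correctly identify the whistle. Give a confidence interval that reflects the RDS design, for example from an RDS bootstrap. Report the unweighted ratio in Chapman form as a sensitivity analysis. State that N refers to the 15-day distribution period.

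The cost is analysis wording, since network size and token identification are already to be collected. The downside is a wider interval, as the last step of the working shows.

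Two limits should be stated with the result. Weighting removes only the dependence that runs through reported network size; any link between token receipt and enrolment through NGO contact would remain. Reading N as the size during the distribution period also assumes that later arrivals among participants are few, or are identified and left out of p_w. The mobility items already in the questionnaire may help to judge this.
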